#### 16.1.1 Adverse events (AE)

An adverse event is defined as a medical event that occurs from the time the patient receives the isotope injection to 90 minutes thereafter.

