#### 10.5 DAY 5 (DAY 4 TO 7) – FOLLOW UP

At least three days after the second series of measurements the investigator notes any complications in the CRF. A copy of monitoring hospital records are taken and patient identity concealed. These are attached to the CRF.

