#### 16.1.2 Adverse reactions (AR)

An adverse reaction is a harmful and unintended medical response to a medical product. For an AE to become an AR, the suspected association between the product and the reaction must at least be possible.

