#### 16.1.3 Serious adverse events (SAE)

An unintended medical event that at any dose:

- Results in death
- Is life-threatening
- Causes hospitalization or prolongation of existing hospitalization
- Results in persistent or temporary disability
- Results in congenital damage or malformation

- Is serious by other means

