#### **16.1.4 Suspected unpredicted serious adverse events (SUSAR)**

A reaction or event that is unexpected, serious, suspected to be caused by the treatment and that is not previously described.

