#### **16.2.2 Assessment of causality**

**Likely:** Clinical event, including abnormal laboratory analyzes, which occur within a reasonable time after administration of the intervention / study product. Unlikely that the event can be attributed to underlying disease, other drugs or other treatment.

**Possible:** Clinical event, including laboratory analyzes, which occur within a reasonable time after administration of the intervention / study product. The event might be explained by underlying disease or other drugs.

**Unlikely:** Clinical event, including abnormal laboratory analyzes, which can temporarily be related to the administration of the intervention / study product. The event is unlikely related to the intervention / study product and can be explained by other drugs or underlying disease.

**Not possible to classify:** The event cannot be classified because of missing information or that the event is not verified.

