## **17 REPORTING OF ADVERSE EVENTS**

### **17.1 REPORTING ADVERSE EVENTS (AE)**

All undesirable events that occur immediately adjacent to SERALB-125 dose should be considered as an AE and documented in accordance with ICH GCP principles.

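### The adverse-event definition stops 90 minutes after each injection, so a later non-serious tracer reaction has no reporting route or required causality grade, and neighbouring sections use different time limits

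*Protocol*

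**What the plan says.** The time limit is set in section 16.1.1: "An adverse event is defined as a medical event that occurs from the time the patient receives the isotope injection to 90 minutes thereafter". Section 17.1 uses a similar but looser limit: "All undesirable events that occur immediately adjacent to SERALB-125 dose should be considered as an AE". The flow chart in 27.1 marks adverse events on Day 0 and Day 2 and leaves Day 5 blank.

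The neighbouring definitions set no such limit. Section 16.1.2 opens with "An adverse reaction is a harmful and unintended medical response to a medical product" and continues "For an AE to become an AR, the suspected association between the product and the reaction must at least be possible". Section 16.1.3 defines a serious adverse event as "An unintended medical event that at any dose" meets one of the listed seriousness criteria. Section 16.1.4 defines a SUSAR as "A reaction or event that is unexpected, serious, suspected to be caused by the treatment and that is not previously described". The Likely and Possible causality categories in 16.2.2 refer to events "which occur within a reasonable time after administration of the intervention / study product".

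Information on later events is collected all the same. Section 10.4 has postoperative complications documented in the CRF at the second measurement, and 10.5 adds: "At least three days after the second series of measurements the investigator notes any complications in the CRF". Section 18.1 keeps monitoring records until three days after the second series.

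Section 16.1 exempts anticipated effects of anaesthesia or surgery from reporting. Its reason is that they are unrelated to the isotope.

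**The concern.** The study gives a radiolabelled product twice, about two days apart, to patients who have major surgery in between. The first window closes at about the time anaesthesia starts, since section 10.3 brings the patient in about two hours beforehand. From then until the second injection, and again from 90 minutes after that injection, no event can be an adverse event under 16.1.1.

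A mild or moderate reaction in those periods would appear at most as a complication in the CRF, and nothing requires anyone to ask whether the tracer could have caused it. A final statement that no adverse events were related to the product would then cover only the two 90-minute windows. Because the definitions can be read in two ways, different staff could also classify the same late serious event differently.

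**Working it through.** No power or alpha figure is involved. The check compares the definitions, with simple arithmetic on the window.

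**1. Length of the window.** Inputs: 90 minutes per injection (16.1.1) and two injections (9.1).

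- Adverse-event time per patient: 2 × 90 min = 180 min = 3 h.
- Nominal follow-up, Day 0 to Day 5: 5 × 24 h = 120 h, so 3 / 120 = 2.5%.
- With the permitted Day 4 to Day 7 range for the last visit: 3 / 96 = 3.1% to 3 / 168 = 1.8%.
- Nominal gap between the end of the first window and the second injection: 48 h − 1.5 h = 46.5 h. With the second measurement on Day 1 to Day 4, this is 24 − 1.5 = 22.5 h to 96 − 1.5 = 94.5 h.

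**2. Time limit in each place.**

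| Place | Time limit stated |
|---|---|
| 16.1.1, adverse event | 90 minutes after injection |
| 17.1, adverse-event reporting | Close to the dose, no figure |
| Flow chart, adverse events | Day 0 and Day 2 only |
| 16.1.2, adverse reaction | None in the first sentence; the second starts from an adverse event |
| 16.1.3 and 17.2, serious adverse event | No onset limit; 24 h reporting clock from awareness |
| 16.1.4 and 17.3, SUSAR | No onset limit; 7 or 15 days from the sponsor's knowledge |
| 16.2.2, causality | Reasonable time after administration |
| 10.5, complications | At least three days after the second series |

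**3. Outcome for three kinds of event.** Under reading A each definition stands alone. Under reading B reactions and serious events are subsets of adverse events.

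| Event | Reading A | Reading B |
|---|---|---|
| Non-serious, within 90 minutes | Adverse event, assessed under 16.2 | Same |
| Non-serious, later, tracer suspected | Not an adverse event. Can meet the first sentence of 16.1.2, but section 17 has no route for a non-serious reaction | Neither adverse event nor adverse reaction |
| Serious, later, unexpected, tracer suspected | Serious adverse event and SUSAR, reportable under 17.2 and 17.3 | The 90-minute limit carries over and the event falls outside |

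The second row fails under both readings. The third depends on the reading, and the protocol does not say which applies. Reading A also leaves serious events with no stated end of collection.

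**4. Whether a grade is required.** Section 16.2 is headed as the assessment of adverse events, and 16.2.1 requires classification of each adverse event. The category wording in 16.2.2 speaks of clinical events more broadly, but no sentence extends the duty to grade to complications noted under 10.4 or 10.5. A late complication may be graded, but nothing requires it.

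**The case against.** The short window has a stated reason. Section 16.1 explains that every patient will have events that would count as adverse elsewhere. The 90 minutes also match the measurement period (9.1) and the monitored period (15.1). Late events are not lost from the record, because complications are documented on Day 2 and Day 5 and copies of records are attached. The blank Day 5 cell in the flow chart agrees with 16.1.1 and is not a separate error. All of this stands. It does not answer the point, because the exemption in 16.1 already separates surgical effects from tracer effects, and noting a complication is not the same as assessing its cause.

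Two stronger conclusions are tempting, and the documents do not support them.

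- A reader might infer that a late serious reaction can never be classified or reported. Sections 16.1.3, 16.1.4, 17.2 and 17.3 set no onset limit, and the first sentence of 16.1.2 defines a reaction without reference to an adverse event. The second sentence says when an adverse event becomes a reaction; it does not say that nothing else can be one. Nor does 16.2.2 bar grading after 90 minutes.
- A reader might take the 97.5% of the nominal 120 hours that lies outside the window (1 − 0.025) as the share of reactions missed. It is a share of clock time only. The protocol gives no rate or timing of reactions to the tracer.

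**Conclusion.** The concern holds for late non-serious reactions. Under either reading they have no adverse-event status, no reporting route and no required causality grade. For late serious events the finding is narrower: they are reportable if the definitions are read literally, but 16.1.2 allows a reading that excludes them, and 16.1.1, 17.1 and 16.2.2 use three different time standards.

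The defined window is 3 h per patient. How many reactions this would miss cannot be estimated from the protocol, and in a pilot of at most 16 patients it may well be none. The statement that no grade is required rests on reading 16.2 as limited to adverse events, as its heading and 16.2.1 indicate. The kinetic endpoints and their analysis are unaffected. The weakness is in the safety record, and it should be corrected because the needed information is already collected.

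**What to change.** - State one collection period and use it throughout 16.1.1 to 16.1.4, 16.2.2, 17.1 to 17.3, 10.5 and the flow chart. It should cover the follow-up already performed. Changing 16.1.1 alone would create a new conflict with 17.1.
- State whether adverse reactions, serious adverse events and SUSARs are subsets of adverse events or stand on their own.
- Keep the exemption in 16.1 for anticipated effects of anaesthesia and surgery.
- Require a causality grade under 16.2.2 for each complication already noted on Day 2 and Day 5. Handle those graded Possible or Likely as adverse reactions, and say in section 17 how non-serious ones are reported.
- Align the Day 5 column of the flow chart with the period chosen.

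The cost is wording in these sections and one causality entry per complication in at most 16 patients. No visit, sample or record copy is added. The drawback is that, after this kind of surgery, most of those entries will probably be graded Unlikely.

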#### 16.1.2 Adverse reactions (AR)

An adverse reaction is a harmful and unintended medical response to a medical product. For an AE to become an AR, the suspected association between the product and the reaction must at least be possible.

#### 16.1.3 Serious adverse events (SAE)

An unintended medical event that at any dose:

- Results in death
- Is life-threatening
- Causes hospitalization or prolongation of existing hospitalization
- Results in persistent or temporary disability
- Results in congenital damage or malformation

- Is serious by other means

#### **16.1.4 Suspected unpredicted serious adverse events (SUSAR)**

A reaction or event that is unexpected, serious, suspected to be caused by the treatment and that is not previously described.

### **16.2 ASSESSMENT OF ADVERSE EVENTS**

#### **16.2.1 Assessment of severity**

Each adverse event will be classified by the investigator as mild, moderate or severe.

**Mild:** The event does not affect the person's normal life.

**Moderate:** The event causes deterioration of function but does not affect health. The event gives discomfort and/or causes inconvenience.

**Severe:** The event causes deterioration of function or working capacity or endanger the health of the person.

#### **16.2.2 Assessment of causality**

**Likely:** Clinical event, including abnormal laboratory analyzes, which occur within a reasonable time after administration of the intervention / study product. Unlikely that the event can be attributed to underlying disease, other drugs or other treatment.

**Possible:** Clinical event, including laboratory analyzes, which occur within a reasonable time after administration of the intervention / study product. The event might be explained by underlying disease or other drugs.

**Unlikely:** Clinical event, including abnormal laboratory analyzes, which can temporarily be related to the administration of the intervention / study product. The event is unlikely related to the intervention / study product and can be explained by other drugs or underlying disease.

**Not possible to classify:** The event cannot be classified because of missing information or that the event is not verified.

## **17 REPORTING OF ADVERSE EVENTS**

### **17.1 REPORTING ADVERSE EVENTS (AE)**

All undesirable events that occur immediately adjacent to SERALB-125 dose should be considered as an AE and documented in accordance with ICH GCP principles.

### **17.2 REPORTING SERIOUS ADVERSE EVENTS (SAE)**

Serious adverse events should be reported to the sponsor on a special SAE form within 24 hours of the investigator learned of the SAE. Follow-up information that describes the outcome and management of the SAE must be reported as soon as the information is available. The original document should be placed in the CRF.

### **17.3 REPORTING SUSPECTED UNPREDICTED SERIOUS ADVERSE EVENTS (SUSAR)**

The sponsor is responsible for ensuring that all relevant information about suspected, unexpected, serious adverse reactions are recorded and reported to EudraVigilans and to relevant ethical review boards.

SUSARs that are fatal or life-threatening shall be reported to EudraVigilans as soon as possible and no

later than 7 days after the incident has become known to the sponsor. Relevant follow-up data should then be forwarded within another 8 days. Other SUSARs shall be reported as soon as possible and no later than 15 days after they arrived at Sponsor's knowledge. For this type of reporting, the sponsor has contracted Karolinska Trial Alliance, which will be responsible for such reports.

## 17.4 FOLLOW UP OF ADVERSE EVENTS

The principal investigator (physician) will be present or immediately available during the whole experiment and will make assessment of the severity if adverse event occurs. Adverse events not related to the study, will be followed up within the routine framework of the clinic.

# 18 STATISTICS AND DATA MANAGEMENT

## 18.1 DATA MANAGEMENT

All laboratory values will be printed from the patient record (Take Care, TC) de-identified and attached to the CRF. All values of the vital parameters during and after the injection will be documented directly on a coded anesthesia paper record by the research nurse or the investigator. This journal is a part of the CRF. At the end of the surgical procedure, the anesthesia records will be copied and made anonymous and attached to the CRF. Other documents that are stored in the CRF for coding and de-identification are: pre-anesthetic assessment, medical record, medication list from TC, surgery report and monitoring records until 3 days after the second series of measurements with isotopes.

Data from the mass spectrometer measurements of phenylalanine will be exported as a data sheets via a USB stick.

All the data regarding end-points will be added in an Access database that is locked when data collection is complete.

De-identified and coded patient demographics preoperatively, per-operatively and post-operatively will be prepared and included in the Access database.

## 18.2 STATISTICAL ANALYSIS

There is evidence that the rate of synthesis of albumin, measured as fractional or absolute synthesis rate, increase in states of general inflammation that occurs after this kind of surgery. Furthermore, albumin capillary leakage increases as measured by the fraction of albumin in the blood and the total outflow of albumin from the blood. The endpoint is the change in these four parameters. To take the step from fractions to absolute values requires an assessment of plasma volume, P-albumin and body weight. All data will be presented as mean with standard deviation (SD) or as median and range of data if not normally distributed. The changes in the variables will be tested with two-sided paired t-test alternative Wilcoxon's test with a significance level of 0.05.

Furthermore, the mutual correlations between the four kinetic albumin parameters as well as with P-albumin will be calculated and presented with correlation coefficients. That changes in capillary leakage and synthesis rate could correlate is reasonable, but not previously described.

Correlation between the above kinetic albumin variables and degree of SIRS (HR, LPK, temperature, respiratory rate) including CRP will be explored. It is reasonable to believe that the degree of inflammation affects the change of albumin variables. Influence of pre-operative weight loss on albumin preoperative kinetic variables will also be analyzed, because weight loss could be a factor that already pre-operatively affects albumin kinetic variables. Correlations will be reported as Pearson correlation coefficient  $r$  or Spearman's rank correlation  $r_s$  depending on the data's nature.

Demographic preoperative data such as age, height, weight, BMI, gender, some routine lab, preoperative weight loss, duration of pancreatic disease, diagnoses, current medications, completing

chemotherapy and ASA class will be presented as numbers, averages and standard deviation, or median range depending on the data's nature. Likewise per- and postoperative demographics such as surgery haemorrhage, supplied anesthetics including epidural anesthesia (doses, number), given fluid infusions including blood products (ml), surgical procedure, post-operative medical or surgical complications, postoperative drug delivery, including the epidural, and laboratory test according to routine will be reported.

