### **7.2 SECONDARY QUESTION**

Do changes in albumin kinetic variables (P alb, FSR, ASR, TER and Jalb) correlate to the degree of SIRS or the increase in CRP?

Do albumin kinetic parameters correlate with each other before or after surgery?

Does pre-operative body weight loss correlate with pre-operative albumin kinetic parameters?

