#### 11.3 ANALYSIS

The step from fractional synthesis rate (FSR %/d) to absolute synteshanstighet (ASR mg/kg/d) is taken by multiplying FSR by the intravascular albumin mass (IAM, g), which in turn is a product of the P- albumin and plasma volume (PV) and finally dividing the result by the body weight. Similarly, the total mass flow rate of albumin from the blood (Jalb) is calculated from the transcapillary albumin leakage (TER).

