### 18.3 DETERMINATION OF THE NUMBER OF SUBJECTS

In paragraph 1 of this protocol, we specify the total number of patients to 16. The higher number is a way to keep abreast of any shortfall, but the analysis are so costly that the intention is to cancel the recruitment when we reached the 10 evaluable patients.

With 10 evaluable patients there is a power of 80% to detect a difference of effect size 1 with a 2-sided t-test and a significance level of 5%. The absolute albumin synthesis rate has been measured at  $131 \pm 21$  mg/kg/day in healthy subjects (control group) where intra-individual standard deviation for repeated measurement after 2.5 hours was 11 mg/kg/day [Barle 2002], which can be perceived as the uncertainty of the method in this specific and very controlled situation. With repeated measurements on ICU patients with 5-day intervals corresponding values were  $233 \pm 67$  and 70 mg/kg/day [Barle 2001a]. There is reason to believe that in this case we will fall between these figures. If the variation of the change is 30 mg/kg/day a difference in the absolute synthesis rate of 30 mg/kg/d can be detected with 80% power. We believe this to be a clinically relevant change.

Some patients can be expected to have increased capillary leakage (TER) in the basal measurement (before surgery) due to hypertension, diabetes and malignancy, but this is less of a problem when the patients serve as their own controls.

Ten patients, give an 80% power to detect a correlation between, for example, capillary leak and synthesis rate if  $r$  is greater than 0.71 ( $r^2 \geq 0.5$ ) with a two-sided test and a significance level of 5%.

We have not found any published measurements of neither synthesis rate or capillary leakage of albumin in this patient group. Any assumption regarding the distribution and change in albumin kinetic parameters thus becomes unsure. There is a risk that this pilot study proves to be a bit too weak in power, but it is very resource intensive measurements, and if so we can submit an amendment to expand the investigation. The large number of correlations mentioned above must be seen against the background that this is an exploratory pilot study of physiological changes in scheduled surgery. There is thus an intention that the study is mainly hypothesis generating.

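### Three planned correlations among leakage, synthesis and P-albumin share a built-in factor, so a test against r = 0 is not calibrated for them

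*Protocol*

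**What the plan says.** Section 7.2 of the protocol asks, as a secondary question: "Do albumin kinetic parameters correlate with each other before or after surgery". Section 18.2 answers it by correlating everything with everything: "the mutual correlations between the four kinetic albumin parameters as well as with P-albumin will be calculated and presented with correlation coefficients". The four parameters are FSR, ASR, TER and Jalb. Pearson or Spearman coefficients will be reported, and 18.2 remarks that a link between the changes in leakage and in synthesis is plausible but so far unreported.

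Section 11.3 fixes how the absolute rates are built. ASR comes from "multiplying FSR by the intravascular albumin mass (IAM, g), which in turn is a product of the P- albumin and plasma volume", followed by "finally dividing the result by the body weight". The mass flow is handled the same way: "the total mass flow rate of albumin from the blood (Jalb) is calculated from the transcapillary albumin leakage (TER").

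Section 18.3 attaches a significance test to these correlations: "Ten patients, give an 80% power to detect a correlation between, for example, capillary leak and synthesis rate", for r above 0.71, two-sided at 5%. It does not say which measure of leakage or of synthesis is meant. It excuses the large number of correlations by the exploratory aim, but says nothing about variables that contain one another.

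**The concern.** A correlation test asks whether r differs from zero. That is the right question only if r would be zero when the two quantities have nothing to do with each other. When one variable is a multiple of the other, or both are multiples of a third, r is above zero by construction. A patient with a large albumin pool per kg gets both a high ASR and a high Jalb, even if FSR and TER are unrelated.

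At stake is what the pilot hands on. Section 5.1 describes it as the first step of a programme leading to a larger study, and 18.3 calls it mainly hypothesis generating. A chance finding tends to disappear on replication. A shared-factor finding tends to recur in any later study that uses the same formulas, so the wrong lead could persist.

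**Working it through.** **Inputs from the protocol.** n = 10 evaluable patients (9.1), two-sided 5% (18.3), and the 11.3 formulas:

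- ASR = FSR × P-albumin × PV / weight
- Jalb = TER × P-albumin × PV / weight

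Section 18.3 gives spread for ASR only: 131 ± 21 in healthy subjects (21/131 = 16%) and 233 ± 67 in ICU patients (67/233 = 29%). It expects this study to lie between them.

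**Assumed.** The CVs of FSR, TER, P-albumin and PV/weight, which the protocol does not give, and mutual independence of these four, which is what no biological link means here.

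**The plan's own figure.** With df = 8 and noncentrality √(10 × 0.71² / (1 − 0.71²)) = √(5.041/0.4959) = 3.19, power is 79.7%, which matches the stated 80%. This is a fixed-predictor calculation. With both variables random, exact two-sided power is about 70%. Either way the reference value is r = 0, and significance at n = 10 means |r| > 0.632.

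**Counting pairs.** Five variables give 5 × 4 / 2 = 10 pairs.

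- Sharing a factor (5): FSR–ASR (FSR), TER–Jalb (TER), ASR–Jalb (P-albumin × PV / weight), ASR–P-albumin and Jalb–P-albumin (P-albumin).
- Sharing none (5): FSR–TER, TER–ASR, FSR–Jalb, FSR–P-albumin, TER–P-albumin.

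**Expected r under independence.** For modest CVs, squared CVs add, so approximately:

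- r(ASR, Jalb) = pool² / √[(FSR² + pool²)(TER² + pool²)], where pool² = P-albumin² + (PV/weight)²
- r(ASR, P-albumin) = P-albumin / √(FSR² + pool²)

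For FSR and TER at 20% and the two pool components at 15%: pool² = 0.0225 + 0.0225 = 0.045, so r(ASR, Jalb) = 0.045/0.085 = 0.53 and r(ASR, P-albumin) = 0.15/√0.085 = 0.51. Simulation gives medians of 0.55 and 0.53.

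**False-positive rates.** 40,000 simulated trials of 10 patients, independent lognormal components, Pearson test:

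| FSR and TER CV | P-albumin CV | PV/weight CV | resulting ASR CV | ASR–Jalb: median r, significant | ASR–P-albumin significant | at least one of the three |
|---|---|---|---|---|---|---|
| 30% | 5% | 5% | 31% | 0.05, 5% | 7% | 19% |
| 16% | 5% | 10% | 20% | 0.34, 15% | 11% | 31% |
| 25% | 10% | 10% | 29% | 0.25, 11% | 17% | 36% |
| 16% | 10% | 10% | 21% | 0.46, 25% | 28% | 55% |
| 20% | 15% | 15% | 30% | 0.55, 37% | 35% | 65% |
| 16% | 15% | 15% | 27% | 0.65, 54% | 42% | 76% |

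Jalb–P-albumin behaves like ASR–P-albumin. With FSR and TER at 15% and pool components at 4% (ASR CV 16%, the healthy value), ASR–Jalb is significant in about 6%. For comparison, three independent tests at 5% would give at least one in 1 − 0.95³ = 14%.

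The ASR spread does not settle the size: rows with ASR CV 29% and 27% give 11% and 54% for ASR–Jalb. What matters is how the spread divides between the rate and the pool.

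**Controls.** FSR–TER, TER–ASR and FSR–Jalb stay at 5%. The same simulation on changes gives nearly the same rates (36% against 37% for ASR–Jalb in the 20%/15%/15% case).

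**The case against.** The strongest reply has four parts.

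1. **Tautologies.** FSR–ASR and TER–Jalb relate a rate to its own rescaling, and anyone who reads 11.3 can see it. This stands. A reader might infer that the secondary question would be answered yes whatever the physiology, since with a pool CV of 14–19% at least one of the five coupled pairs is significant in 97–99% of simulated trials. But with a pool CV of 14% those two pairs alone account for 90–98%, and nobody would report them as discoveries.

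2. **The leakage–synthesis link.** A reader might also infer that this link would be found falsely. In most of the cases above ASR–Jalb is not significant. Three of the four leakage–synthesis pairings (TER–FSR, TER–ASR, Jalb–FSR) share no factor, and 18.3 itself labels leakage as TER. This stands too, although 18.2 also describes leakage by total outflow, so ASR–Jalb remains a natural reading.

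3. **Unknown spreads.** The size rests on CVs that the protocol does not supply, and with a tight albumin pool the inflation nearly vanishes. This is correct and limits any claim about size. It does not alter the algebra.

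4. **Exploratory status.** Section 18.2 only says that coefficients are calculated and reported, a test appears only in 18.3, and the study is exploratory. This answers part of the point. The caveat in 18.3 concerns the number of correlations, which is multiplicity. It does not cover a coefficient biased away from zero, and that bias is present even if no p-value is printed.

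**Conclusion.** The point holds as a should-fix. That five of the ten pairs share a factor is exact and follows from 11.3. For ASR–Jalb, ASR–P-albumin and Jalb–P-albumin, r = 0 is the wrong reference value.

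The inflation ranges from almost none to several times the nominal 5%. The ranges of 5–6% up to 37% (ASR–Jalb), 7–35% (each P-albumin pair) and 19–65% (any of the three) describe selected combinations and are not bounds, as the last table row shows. They assume n = 10, independent lognormal components and CVs that are not in the protocol.

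The documents do not support going further. The paired tests of the primary endpoints are untouched, the uncoupled correlations are sound on this count, and the correlations serve a secondary, exploratory question.

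**What to change.** In 18.2:

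- Make FSR–TER the main leakage–synthesis correlation.
- Keep the other uncoupled pairs: TER–ASR, FSR–Jalb, and P-albumin with FSR and with TER.
- Do not test the five coupled pairs against r = 0. Present them as descriptive only, and state the factor each pair shares. ASR–Jalb still has descriptive value, because whether the mass made and the mass leaving plasma move together is a fair question.
- If inference on ASR–Jalb is wanted, use the partial correlation of log ASR and log Jalb given log(P-albumin × PV / weight). It held 4.9–5.4% in simulation. Since log ASR minus the log pool is log FSR, and likewise for Jalb and TER, this amounts to correlating log FSR with log TER adjusted for the pool.

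In 18.3, name FSR and TER in the correlation example.

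The cost is a few sentences and no new data. The small downside is having no significance test on the five coupled pairs.
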